## Abstract

**Introduction:**

Piling evidence suggests that a higher level of prestroke physical activity can decrease stroke severity, and reduce the risk of poststroke mortality. However, prior studies have only included ischaemic stroke cases, or a majority of such. We aim to investigate how premorbid physical activity influences admission stroke severity and poststroke mortality in patients with intracerebral haemorrhage, compared with ischaemic stroke. A prespecified analysis plan counteract some inherent biases in observational studies, and promotes transparency.

**Methods and analysis:**

This is a statistical analysis protocol for a matched cohort study, including all adult patients with intracerebral haemorrhage, and matched ischaemic stroke controls, treated at Sahlgrenska University Hospital in Sweden between 1 November 2014 and 30 June 2019. All patients have been identified in the Väststroke register, and the data file has been sent for merging with national registries. The follow-up of time for survival will be approximately 2–7 years. The sample size calculation indicates that a minimum of 628 patients with intracerebral haemorrhage is needed for power of 80% at an alpha level of 0.01. Multiple imputation by chained equations will be used to handle missing data. The entire cohort of patients with intracerebral haemorrhage will be matched with consecutive ischaemic stroke controls (1:3 ratio) using nearest neighbour propensity score matching. The association between prestroke physical activity and admission stroke severity will be evaluated using multivariable ordinal regression models, and risk for all-cause mortality will be analysed using multivariable Cox proportional-hazards models. Potential confounders include age, ethnicity, income, educational level, comorbidity, medical treatments, alcohol-related disorders, drug abuse and smoking.

**Ethics:**

Data collection for the Physical Activity Pre-Stroke In GOThenburg project was approved by the Regional Ethical Board on 4 May 2016. An additional application was approved by the National Ethical Review Authority on 7 July 2021.

Strengths and limitations of this studyA prespecified sample size calculation and statistical analysis plan decrease bias in observational research.The novel relationship between prestroke physical activity and outcomes after intracerebral haemorrhage will be studied in a large sample.Comprehensive covariate adjustment will enhance the reliability of the results.The retrospective analysis of registry data is a limitation of the study.Self-reported assessments of prestroke physical activity introduce recall bias, which is another limitation of the study.

## Introduction

Observational studies are of great value in cases when a randomised controlled trial would be unethical, impractical or untimely. Observational studies are, however, subjected to several types of selection and reporting bias, which can lead to a lack in reproducibility. The reliability of observational data can be enhanced by emulating principal design aspects of randomised trials.^1^ Prespecified eligibility criteria, a priori sample size estimation, definition of exposure and outcome measures, a standardised follow-up period, and a statistical analysis plan may counterbalance some inherent limitations of the observational study design and promote transparency.^2^

Physical activity is an example of exposure that is hard to study in a randomised, controlled setting. The relationship between premorbid physical activity and admission stroke severity, as well as poststroke mortality has been analysed in several observational studies, with varying results. The majority of prior studies have found that prestroke physical activity reduce stroke severity,^3–8^ in-hospital mortality,^8^ cardiovascular mortality^9^ and all-cause mortality.^9–12^ However, some studies found no associations between physical activity and stroke severity,^13 14^ or poststroke mortality after covariate adjustment.^15 16^ These studies differ in data collection strategies, sample sizes, physical activity assessments and statistical analyses. Moreover, none of the prior studies have investigated the association between prestroke physical activity and stroke severity or mortality in the subgroup of patients with intracerebral haemorrhage (ICH).

Here, we present a statistical analysis plan, and give the rationale for an observational, matched cohort study part of the Physical Activity Pre-Stroke In GOThenburg (PAPSIGOT) project. We also provide a narrative discussion for potential confounding factors to the effect of prestroke physical activity on outcomes after ICH. This study protocol follows the guidelines for reporting of statistical analysis plans in clinical trials, published in the Journal of the American Medical Association.^17^

### Research objectives

(1) To investigate the relationship between prestroke physical activity and admission stroke severity in patients with ICH, compared with patients with ischaemic stroke. (2) To investigate how prestroke physical activity influence the risk of mortality after ICH, in comparison to ischaemic stroke.

## Methods

This is a statistical analysis protocol for a matched cohort study. Prestroke physical activity is the main independent variable. Admission stroke severity and all-cause mortality are the outcome variables of interest. All adult patients with ICH and ischaemic stroke, treated at Sahlgrenska University Hospital between 1 November 2014 and 30 June 2019 have been identified in the Väststroke register. The comprehensive stroke units at Sahlgrenska University Hospital has a catchment area of 700 000 people, and patients who had a stroke in nearby regions requiring thrombectomy or neurosurgical monitoring are transported to this hospital. All persons with stroke in Sweden have equal access to tax-funded healthcare services, which ensures the representativeness of this sample.

### Data collection and management

Prestroke physical activity and acute stroke severity assessments were collected from the Väststroke register, and cross-references with medical records to minimise missing data. Physical activity was assessed using the four-level Saltin-Grimby Physical Activity Level Scale (SGPALS).^18 19^ Acute stroke severity was assessed using the National Institutes of Health Stroke Scale (NIHSS).^20^ The data collected from the Väststroke register has been sent for merging with national registries. Information regarding prestroke conditions and treatments will be collected from the Swedish National Stroke Registry (Riksstroke). Country of birth will be collected from the Swedish Multi-Generation register, and socioeconomic variables will be collected from the Longitudinal Integration Database for Health Insurance and Labour Market Studies held by Statistics Sweden. Comorbidities will be collected from the National Patient Registry, and mortality rates will be collected from the Swedish Cause of Death registry, held by the National Board of Health and Welfare. All-cause mortality and cerebrovascular mortality will be recorded for all patients until October 2021, which allow for a minimum follow-up of 2 years.

The data management started on 17 May 2021 after submission of this protocol. The final data was recived on 19 October 2021. Patients without a Swedish personal identification number, and patients with non-specified aetiology will be excluded. The final sample is will consist of 763 patients with ICH.

Continuous variables will be either mean-centred or dichotomised when appropriate. For ordinal variables, categories with limited observations will be merged on the base of clinical reasoning. All variables and data sources are listed in table 1. The categories of SGPALS will be collapsed into inactive (SGPALS level 1) and physically active (SGPALS levels 2–4) for all analyses. NIHSS scores will be categorised based on distributional assumptions.^6^ The weighted Charlson Comorbidity Index will be calculated, and applied as a four-level ordinal variable using the ICD-10 diagnoses specified in table 1. The 1-year mortality risk described by Charlson *et al* was 12% for patients with 0 points, 26% for 1–2 points, 52% for 3–4 points and 85% for ≥5 points.^21^

**Table 1 T1:** Registers and variables included in the study

The väststroke register	
Age	Mean centred or dichotomised.
Sex	Female/male.
Physical activity assessment (SGPALS)	Mostly sedentary (level 1); light physical activity such as walking ≥4 hours/week (level 2); moderate physical activity such as running ≥2 hours/week (level 3); hard physical training for competition sports several times per week (level 4).
Stroke severity assessment (NIHSS)	Mild stroke (NIHSS 0-5), moderate stroke (NIHSS 6-14), and severe stroke (NIHSS >14).

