**The LISA register**	
Country of birth	Born in Sweden/born outside of Sweden.
Income	Mean centred or dichotomised.
Educational level	Primary school (<10 years), secondary school (10–12 years) and postsecondary or university education (>12 years).

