### Statistical analyses

Data will be analysed using R, V.4.0.2 (R Core Team. R: A language and environment for statistical computing. R Foundation for Statistical Computing, Vienna, Austria.), and SPSS Statistics for Windows, V.27.0 (released on 2018; IBM). All statistical testing will be interpreted at a two-tailed significance level of 0.01 to adjust for multiple comparisons.

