### Regression models

We will conduct separate models for haemorrhagic and ischaemic stroke cases, respectively. All models will be adjusted for potential confounders. The association between prestroke physical activity and admission stroke severity will be evaluated using multivariable ordinal regression models.^28^ For the ordinal regression, NIHSS scores will be trichotomised. A subgroup analysis will be performed for patients with first-time ICH. Prior to the analyses, absence of multicollinearity, and the proportional odds assumption will be checked. Diagnostics will be performed using surrogate residuals.^29^

The association between prestroke physical activity and all-cause mortality will be evaluated using multivariable Cox proportional-hazards models.^30^ Additional models will be fitted adjusted for admission stroke severity.^31^ Model diagnostics will be applied to evaluate violations of the proportional hazards assumption, random censoring and functional forms of continuous covariates.^32^ Furthermore, outlying and influential observations will be checked for all models.

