**Figure 1 F1:**
[figure not shown]
Directed acyclic graph for confounders to the effect of physical activity on outcomes after intracerebral haemorrhage (stroke severity and poststroke mortality). Solid lines indicate the relationships between covariates, and the dotted line indicate the causal effect of physical activity.

Degenerative vascular changes are frequent in the ageing population. In addition to being a risk factor for all stroke, higher age has been identified as an important predictor of disability, and decreased long-term survival in ICH^33 34^ A person’s age also influences the probability of being physically active,^35^ and should therefore be considered a confounding factor. Sex, however, did not significantly influence the severity of haemorrhagic stroke in a meta-analysis of eight population‐based stroke incidence studies.^36^

Socioeconomic status-related differences influence haemorrhagic stroke severity, but could partly be explained by differences in comorbidities, disparity in health and care services, ethnicity, stress, job strain and life style factors. Income, education and living alone have been associated with mortality following the acute phase of stroke.^37^ Low income was found to increase the absolute risk of death at 3 months after ICH, and the effect was largely mediated by initial stroke severity.^38^ In adulthood, socioeconomic variables are associated with the propensity of being physically active.^39^ Among young people, a recent study found that haemorrhagic stroke survivors of African and Hispanic ethnicity have better outcomes compared with those of Caucasian descent.^40^ In the current study, country of birth will be used as a surrogate measure for ethnicity.

Active cigarette smoking has been associated with increased stroke severity,^41 42^ and premorbid alcohol consumption has been identified as independent determinant of functional status and mortality after ICH.^43^ Cigarette smoking and physical activity are intuitively incongruent behaviours, and both positive and negative associations has been described.^44^ Likewise, alcohol consumption has in some studies been found to be a contributor to sedentary behaviour.^45^

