In conclusion, the following potential confounders will be collected, and adjusted for: age, ethnicity, income, educational level, comorbidity, medical treatments, alcohol related disorders, drug abuse and smoking. The comorbidities accounted for are prior TIA, prior stroke, diabetes, psychiatric disorders and Charlson Comorbidity Index. The medical treatments accounted for are anticoagulant treatment, antihypertensive treatment, antiplatelet treatment and statin treatment.

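### Age and income may be coded as continuous or dichotomised with no rule for choosing; a dichotomised age would leave part of the age confounding in the activity effect

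*Protocol article*

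**What the plan says.** Under Data collection and management, the article sets one rule for all continuous covariates: "Continuous variables will be either mean-centred or dichotomised when appropriate". Table 1 repeats it for age (Väststroke register) and for income (LISA register): "Mean centred or dichotomised". It gives no cut-point for either variable and does not say what would make one coding appropriate. Other entries in the same table, such as education, the Charlson index and NIHSS, have explicit category limits.

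The Confounding variables section gives both sides of the argument for age as a confounder. On the outcome side, "higher age has been identified as an important predictor of disability, and decreased long-term survival in ICH". On the exposure side, "A person’s age also influences the probability of being physically active". The section closes by stating that "the following potential confounders will be collected, and adjusted for: age, ethnicity, income, educational level, comorbidity", and Regression models applies the adjustment to every model. The same section plans a check for the Cox models: "Model diagnostics will be applied to evaluate violations of the proportional hazards assumption, random censoring and functional forms of continuous covariates". Statistical analyses sets the test level: "All statistical testing will be interpreted at a two-tailed significance level of 0.01 to adjust for multiple comparisons".

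**The concern.** The article presents itself as the prespecified analysis plan and gives prespecification as its protection against bias. On the coding of age and income it does speak, but it allows two materially different analyses with nothing to decide between them. This is an open choice written into the plan, not a detail left to another document.

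The two codings do not adjust equally well. With a single cut, everyone on the same side of it is treated as the same age. If older patients are less active and die sooner, active patients are still younger than inactive ones within each half, and activity looks protective even if it does nothing. That is the direction of the study hypothesis.

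**Working it through.** **The plan's own figure.** The article gives no number for residual confounding. Its only related figure, the minimum of 628 patients with haemorrhage, reproduces and does not depend on how age is coded. The Whitehead formula with 60:40 allocation (A = 1.5) and the Table 2 probabilities gives:

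- mean probabilities 0.8005, 0.156 and 0.0435; sum of cubes 0.5168; 1 − 0.5168 = 0.4832
- N = [3(A+1)²/A] × (2.576 + 0.842)² / [(ln 2)² × 0.4832] = 12.5 × 11.68 / (0.4805 × 0.4832) ≈ 629

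**Inputs from the article.** 40% active (60% expected inactive); 763 patients with haemorrhage; 1:3 matching, so 3 × 763 = 2289 ischaemic controls; two-sided alpha 0.01, so 0.5% in the protective direction.

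**Inputs that must be assumed.** The article gives no age distribution, no strength of the age effects and no death rate. Assumed: log odds ratio of being active −0.5 to −0.8 per SD of age; hazard ratio of death 1.6 to 2.0 per SD; log odds ratio of worse severity 0.2 to 0.4 per SD; 50% deaths.

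**Step 1: share of confounding left by one cut.** For normal age with a linear effect, cut so that a fraction p lies above z, the share of age variance left within the groups is 1 − φ(z)²/[p(1−p)].

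- Median cut: 1 − 0.3989²/0.25 = 1 − 2/π = 36.3%, the smallest value for any single cut under this model. Simulation gave 37-38%.
- Cut at the upper 30%: 1 − 0.3477²/0.21 = 42%; simulation 44-49%.
- Cut at the upper 20%: 1 − 0.2800²/0.16 = 51%; simulation 53-60%.

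Departures from that model, by simulation:

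- Left-skewed age: 41-43% at the median, up to 72% at other cuts.
- Other covariates explaining 30-40% of age, median cut: 29-32% of the crude confounding remains (44-49% of what those covariates leave).
- Age effect that is a step exactly at the cut: about 0%.

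**Step 2: consequence with no true activity effect.** 1000 replicates per row, normal age, no other covariates, median split against a linear term. A logistic model of mild versus worse stroke stands in for the ordinal model. Each cell gives the mean ratio and the percentage of runs with a significant protective finding.

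| n | Age→activity, log OR | Age→death, HR | Age→severity, log OR | Mortality, split | Mortality, linear | Severity, split | Severity, linear |
|---|---|---|---|---|---|---|---|
| 763 | −0.5 | 1.6 | 0.2 | 0.927; 3.4% | 1.001; 0.5% | 0.965; 1.0% | 0.999; 0.8% |
| 763 | −0.5 | 2.0 | 0.4 | 0.902; 5.1% | 1.004; 0.6% | 0.930; 1.4% | 0.996; 0.7% |
| 763 | −0.8 | 2.0 | 0.4 | 0.846; 13.3% | 0.995; 0.5% | 0.899; 1.4% | 0.995; 0.1% |
| 2289 | −0.5 | 1.6 | 0.2 | 0.925; 8.1% | 0.998; 0.4% | 0.960; 1.5% | 0.993; 0.5% |
| 2289 | −0.5 | 2.0 | 0.4 | 0.900; 19.0% | 1.003; 0.7% | 0.937; 2.3% | 1.002; 0.3% |
| 2289 | −0.8 | 2.0 | 0.4 | 0.848; 48.6% | 0.997; 0.4% | 0.908; 4.5% | 1.007; 0.5% |

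A separate set of survival simulations (odds ratio of activity 0.55-0.7 and hazard ratio of death 1.8-2.5 per SD of age) gave 0.86-0.94 with the split and 0.98-1.01 with linear age.

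**Step 3: check by hand.** The standard error of the log hazard ratio is about 1/√(events × 0.4 × 0.6): 0.105 for 381 deaths and 0.060 for 1144. A spurious ratio of 0.87 (|ln| = 0.139) is then 1.3 and 2.3 standard errors, or about 10% and 40% false protective findings. A ratio of 0.94 (|ln| = 0.062) gives about 2% and 6%. The result depends strongly on the assumed age effects, so only a range is defensible.

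In the table the bias is the same at both sample sizes, but it reaches significance more often in the larger ischaemic set. A contrast in significance between stroke types could then be misread as a difference in effect.

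**The case against.** The strongest reply is that dichotomising is only one of two permitted codings, and that the other, a mean-centred continuous term, removes the bias under the assumptions used above. That stands. It argues for removing the other option, not for leaving the choice open.

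Several stronger readings are tempting, and the article does not support them:

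- That age will be dichotomised, or that a post hoc choice is intended. The text says neither; the absence of a rule only makes such a choice possible.
- That over a third of the confounding necessarily remains. This holds for normal age, a linear effect and no age-related covariates. The plan adjusts for comorbidity, prior stroke, treatments and more, some of which may track age.
- That the false-positive rates are 10% and 40%. These follow from one value near the unfavourable end of the range.
- That age is the main common cause in the plan's argument. The Confounding variables section ranks nothing, and its age paragraph concerns activity, disability and survival. Admission severity enters only through the Figure 1 caption.
- That the only alternative is a linear term. Mean-centring shifts the origin and does not fix the shape.

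The planned safeguards help less than they may seem to. The Cox check concerns covariates that are still continuous, so it would not reach a dichotomised age. The ordinal models have surrogate-residual diagnostics, but no action is tied to them. The propensity score matching balances haemorrhage against ischaemic stroke, not active against inactive patients, although one sentence of that section speaks of the effect of being active.

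**Conclusion.** The concern holds in a limited form. The plan leaves the coding of age and income open, and one permitted coding adjusts incompletely for a confounder that the plan names. If that coding is used for age, the bias favours activity.

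For mortality it could matter: a spurious hazard ratio of about 0.85 to 0.94, with false protective findings in about 3-13% of runs in the haemorrhage cohort and 8-49% in the ischaemic set, where 0.5% is intended. For severity in the haemorrhage cohort it is small: 1.0-1.4%, against 0.1-0.8% with continuous age, and differences of a few tenths of a percentage point are within simulation error. At n=2289 the severity figure is 1.5-4.5%.

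All these figures rest on assumed age effects, 50% mortality, a median split and no other covariates in the model. For income the same argument applies in principle, but nothing in the article allows a figure.

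**What to change.** Delete the dichotomisation option for age and income, both in the general rule and in Table 1. State in advance that both enter all ordinal and Cox models as continuous variables. A restricted cubic spline with, for example, four knots is a low-cost guard against non-linearity; under a truly linear effect the mean-centred term would already suffice. Both should also enter the propensity score as continuous; the boosted regression planned there needs no spline.

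The cost is a sentence or two of text. A four-knot spline uses three degrees of freedom instead of one, so two extra per variable and four in all. If a dichotomised age is wanted for description or presentation, give its cut-point and keep it out of the adjustment.

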**The Riksstroke register**	
Prior stroke	Yes/no.
Prior transient ischaemic attack	Yes/no.
Atrial fibrillation	Yes/no.
Diabetes	Yes/no.
Regular smoking the year before stroke	Yes/no.
Antihypertensive treatment	Yes/no.
Statin treatment	Yes/no.
Antiplatelet treatment	Yes/no.
Anticoagulant treatment	Yes/no.
**The LISA register**	
Country of birth	Born in Sweden/born outside of Sweden.
Income	Mean centred or dichotomised.
Educational level	Primary school (<10 years), secondary school (10–12 years) and postsecondary or university education (>12 years).
**The NPR**	
Charlson Comorbidity Index: myocardial infarction, heart failure, peripheral vascular disease, dementia, pulmonary disease, connective tissue disease, peptic ulcer disease liver disease, diabetes, Hemiplegia or paraplegia, renal disease, cancer, HIV/AIDS	Low (0 points), moderate (1–2 points), high (3–4 points) and very high (≥5 points) risk. ICD-10 codes: I21, I22, I25.2, I42, I11.0, I13.0, I13.2 I50, I25.5, I65, I70-I74, I77, I73.9, I79.0, R02, F00-F03, F05.1, J40-J47, J60-J67, M05.0-M05.3, M05.8-M06.0, M06.3, M06.9, M32, M33.2, M34, M35.3, K25-K28, K70.2, K70.3, K71.7, K73, k74.0, K74.2-K74.6, K72.9, K76.6, K76.7, K72.1, E10.1, E10.5, E10.9, E11.1, E11.5, E11.9, E13.1, E13.5, E13.9, E14.1, E14.5, E14.9, E10.2-E10.4, E11.2-E11.4, E13.2-E13.4, E14.2-E14.4, G80.0, G80.2, G81, G82, N01-N08, N11, N14-N19, N25, C00-C76, C90, C97, C91-C95, C81-C86, C88, C77-C80, B20-B24
Depression	Yes/no. ICD-10 codes: F32-F33
Psychotic diseases	Yes/no. ICD-10 codes: F20-F29
Alcohol related disorders	Yes/no. ICD-10 codes: F10, K70.1-K70.4, K70.9, K74.0
Drug abuse	Yes/no. ICD-10 codes: F11, T40.0-T40.4, F12, T40.7, F14, T40.5, F15, T43.6, F16, T40.6, F19
**The Swedish cause of death register**	ICD-10 code
All-cause mortality	–
Cerebrovascular mortality	ICD-10 codes: I60-I69

ICD-10, International Classification of Diseases, Tenth Revision; LISA, Longitudinal Integration Database for Health Insurance and Labour Market Studies; NIHSS, National Institutes of Health Stroke Scale; NPR, National Patient Registry; SGPALS, Saltin-Grimby Physical Activity Level Scale.

